### Trial design

1.2

We will conduct a series of personalized N-of-1 trials comparing intervention (**A**, listen to music) and control (**B**, do not listen to music). Each study participant will select a music genre, which they believe will most positively affect their concentration. Each trial consists of two cycles, each containing two treatment periods in a block-randomized sequence of intervention period A and control period B. This yields four possible treatment sequences, *ABAB*, *ABBA*, *BAAB*, and *BABA*. Each treatment period lasts for 3 min, followed by a questionnaire and a 1-min pause. During the treatment periods, the participants perform a digital adaptation of the Stroop test.

Fig. 1Results of Sample Size Calculation.Fig. 1

**(a) fig1a:**
[figure not shown]
Sample size calculation with fixed $\sigma^{2}=0.05$.

**(b) fig1b:**
[figure not shown]
Confirm Power for different values of $\sigma^{2}$.

## Methods

2

### Participants

2.1

#### Study setting

The study will be conducted at the Hasso Plattner Institute in Potsdam, Germany. A designated room will be prepared with necessary equipment, including a 2.1 speaker system, screen, mouse, and keyboard, to facilitate the study procedures. Participants will be provided with sensors that are connected to a computer system for data collection. Before the study start, the room will be adequately ventilated to ensure a suitable environment. The participant will be alone in the room during the intervention and control phases.

#### Eligibility criteria

The study population focuses on adults with a minimum age of 18 years. Inclusion and exclusion criteria are specified in Table 1.

**Table 1 tbl1:** Inclusion and exclusion criteria for the study.

Inclusion criteria	Exclusion criteria
– Fluent in German or English	– Loss of hearing
– Age >=18	– Presence of colorblindness
– Ability to read	– Presence of a neurological disease
– Informed consent	– Presence of epilepsy
	– Presence of a neurodevelopmental disorder
	– Substance abuse (for example, alcohol, drugs, or other)
	– Doctor’s recommendation (or self-assessment) not to perform stressful tasks
	– Participation in another intervention study during the study period

Participants will be asked to give electronic consent, and a physical copy of the consent form will be handed to the participants. Patients or members of the public were not involved in the design, conduct, reporting, or dissemination plans of this research.

#### Sample size

We estimated the required sample size (i.e., number of participants) for testing a population-level average difference in the primary outcome (Stroop test, see Section 2.3) between periods of intervention condition (self-selected music) and control condition (no-music) through simulation studies. The simulation was performed in R using lme4, with seed 123 for reproducibility. We assumed a correct answer rate of 95% in the no-music condition and 96% across all self-selected music conditions based on pilot testing of the digital version of the Stroop task. That is, we assumed a difference in correct answer rate between the conditions of 1%. We assumed 150 observations per 180-second period based on an average response rate of 1.2 s per answer. This yielded about 600 observations per participant across all four periods. Corresponding to those values, we simulated data of our binary outcome variable $Y_{ij}$ (0 = incorrect response, 1 = correct response) for patient i at time point j (subsequently numbered throughout all periods) with a generalized linear mixed model (GLMM) using an intercept of $\beta_{0}$, a fixed effect $\beta_{1}$ of treatment $A_{ij}$ (0 = control condition, 1 = intervention) and we assumed a random effect $u_{i}∼N\left(0,\sigma_{u}^{2}=0.05\right)$ for each individual: (1)$$\beta_{0}=\mathrm{logit}\left(0.95\right)$$$$\beta_{1}=\mathrm{logit}\left(0.96\right)-\mathrm{logit}\left(0.95\right)$$$$p_{ij}={\mathrm{logit}}^{-1}\left(\beta_{0}+\beta_{1}\cdot A_{ij}+u_{i}\right)$$$$y_{ij}=\text{Bernoulli}\left(p_{ij}\right)$$

We simulated 5000 series of N-of-1 trials for each of the following number n of participants: n∈[15,16,…,29,30]. We used a fixed treatment effect $\beta_{1}$, random effect $u_{i}$, and the outcome was randomly drawn from a Bernoulli distribution as shown in Eq. (1). The seed was set to ‘123’.

Next, for each n, we analyzed each of the 5000 series of N-of-1 trials using the generalized linear mixed model (GLMM) defined in Section 2.5. For each n, we estimated the power as the ratio of p-values of the Wald z-test for $\beta_{1}$ that were <0.05 across the 5000 series of trials and calculated the 95% confidence interval for the estimated power based on the Monte Carlo error of the estimated power: (2)$${\text{CI}}_{\text{upper}/\text{lower}}=\text{Power}\pm 1.96\cdot \sqrt{\frac{\text{Power}\cdot \left(1-\text{Power}\right)}{5000}}$$

Fig. 1(a) shows that the estimated power was 80.4% (95% CI: 79.3%–81.5%) with 22 patients and 81.3% (95% CI: 80.2%–82.4%) with 23 patients. In a second step, we iterated over different values of $\sigma_{U}^{2}\in \left\{0.1,0.25,0.5,0.75,1\right\}$ and calculated the corresponding power and its confidence interval. Fig. 1(b) shows that all estimated powers are above the required power of 80%, while only with a standard deviation of $\sigma_{u}^{2}=0.25$ the confidence interval of the power includes 80% (79.7%–81.9%). Hence, we aim for 23 participants in our trial.

On the individual level, assuming 600 available data points, this would allow for the estimation of a treatment effect in the improvement of correct answers from 95% to 96% with a 95% confidence interval width of $2\cdot 1.96\cdot SE\left(\overset{ˆ}{\beta_{1}}\right)=0.117$.

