The sample size calculation for this study is based on generalized linear mixed model (GLMM). The assumed values are based on pilot testing with limited prior evidence and may not fully reflect the true effect size observed during the study. Further, we powered for a small aggregated treatment effect difference of 95% for the no-music condition and 96% for the music condition, which may not be clinically relevant for all participants. Despite this, the individualized nature of the study allows for meaningful intra-participant comparisons, even in the context of such uncertainties.

In this study, the treatment allocation sequence is randomized separately for each participant. Prior to the experimental period, participants will complete seven practice Stroop tasks: two without a time limit and five with a time limit, to familiarize themselves with the task and reduce learning effects during the intervention periods. Washout phases are included between treatment periods to minimize potential carryover effects.

Based on this design, major sequence effects or carryover are not expected. Nevertheless, residual time-related effects such as learning or fatigue cannot be fully excluded. Therefore, although the primary analysis does not explicitly adjust for treatment sequence, sensitivity analyses will explore the robustness of the results with respect to possible temporal trends.

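### The stated individual-level 95% interval width of 0.117 does not follow from the protocol's inputs: it is about 1.55 on the log-odds scale for which it is written, or 0.066 as a risk difference

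*Protocol article*

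**What the plan says.** The Sample size section (2.1) sets the assumptions: "We assumed a correct answer rate of 95% in the no-music condition and 96% across all self-selected music conditions". It defines β₁ as logit(0.96) − logit(0.95), the coefficient of condition in a logistic mixed model. On volume it says: "We assumed 150 observations per 180-second period based on an average response rate of 1.2 s per answer", and "This yielded about 600 observations per participant across all four periods". The Trial design section (1.2) fixes the split within a person: "Each trial consists of two cycles, each containing two treatment periods in a block-randomized sequence of intervention period A and control period B". That is two music and two no-music periods each.

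At its end, the Sample size section turns to the single participant. With 600 data points, it says, the design allows "estimation of a treatment effect in the improvement of correct answers from 95% to 96% with a 95% confidence interval width of" 2 × 1.96 × SE(β̂₁) = 0.117. It shows no working and names no scale other than the one implied by β̂₁.

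The primary research question (1.1) has two parts: the population average and the number of individual participants affected. The Primary analysis section (2.5) plans participant-specific estimates and posterior probabilities of benefit.

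**The concern.** The formula is explicit and its inputs are all in the protocol, so it can be checked. A width of 0.117 around a log odds ratio of 0.234 would run from about 0.175 to 0.292. That would separate one person's effect clearly from zero. With some 5% errors in 300 responses per condition, about 15 errors against 12, such precision is not plausible.

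This is the only statement of individual-level precision in the protocol, and it bears on the individual half of the primary question. A reader who relies on it would expect the trial to show which participants respond. That reader could then take a small number of clear individual results as evidence that few people respond, when the individual data are simply too sparse to show an effect of the assumed size.

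**Working it through.** **Inputs**
- Correct-answer rates: 0.95 without music, 0.96 with music (Sample size).
- Responses: 150 per period and 600 per participant (Sample size); two periods per condition (Trial design), so 300 per condition.
- Width: 2 × 1.96 × SE = 3.92 × SE (Sample size).

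**1. The plan's own figure.** 0.117 implies SE = 0.117 / 3.92 = 0.0298.

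**2. Log-odds scale, as the formula is written.**
- β₁ = ln(0.96/0.04) − ln(0.95/0.05) = ln 24 − ln 19 = 0.2336; odds ratio 1.26.
- SE = √[1/(300 × 0.95 × 0.05) + 1/(300 × 0.96 × 0.04)] = √[1/14.25 + 1/11.52] = 0.396.
- Width = 3.92 × 0.3962 = 1.553. Ratio to the stated figure: 1.553 / 0.117 = 13.3.
- Interval: 0.234 ± 0.777, or −0.54 to 1.01; odds ratio 0.58 to 2.75.
- A simulation of 20,000 single participants gave a mean width of 1.61 and a median of 1.58.

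**3. Risk-difference scale.**
- SE = √[(0.0475 + 0.0384)/300] = 0.0169.
- Width = 3.92 × 0.01692 = 0.066. Ratio to the stated figure: 0.066 / 0.117 = 0.57.
- Interval: 1 ± 3.3 points, or −2.3 to +4.3 percentage points.

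**4. Could any rate give 0.117 for β̂₁?** The log-odds SE is smallest when both rates are 0.5: √[2/(300 × 0.25)] = 0.163, width 0.640. So no pair of rates gives 0.117 with 600 responses split evenly. At 95% and 96%, a width of 0.117 needs about 52,900 responses per condition on the log-odds scale, or about 96 as a risk difference. Neither is 300.

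**5. Other readings tried at 300 per condition.** Log risk ratio 0.070; odds ratio 2.17; back-transformed probability 0.064; log-odds half-width 0.777; log-odds width with the planned N(0, 1) prior 1.44; risk difference with t quantiles 0.146 (2 df) or 0.108 (3 df). None gives 0.117.

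**6. Are the inputs sound?** Yes. With the random-intercept variance of 0.05, the expected information gives SE(β̂₁) = 0.0819 at 23 participants and power Φ(0.2336/0.0819 − 1.96) = 81.4%. The protocol states 81.3%. At 22 participants the result is 79.7%, against 80.4% stated. The fault is confined to the individual-level figure.

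**7. What this means for one participant.** With a true effect of exactly 95% against 96%, z = 0.2336/0.3962 = 0.590. The chance that the 95% interval excludes zero is Φ(0.590 − 1.96) + Φ(−0.590 − 1.96) = about 9%.

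**8. Detectable individual effects by direction.** Exact binomial enumeration, Wald test of the risk difference, 300 per condition, from 95%: power about 86% for 99%, 66% for 90% and 79% for 89%. The normal approximation gives 82%, 65% and 78%.

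**The case against.** The sentence speaks of an improvement from 95% to 96%, which is probability-scale language, although the symbol is β̂₁. If a risk difference was meant, the correct width of 0.066 is narrower than 0.117, and the protocol understates its precision. This stands. The 13-fold overstatement holds only on the log-odds scale, and a reader who inferred that the protocol overstates precision on every scale would go too far.

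The figure also drives nothing. The number of participants comes from the population-level simulation, and no model, prior or decision rule uses 0.117. This stands too, and it limits the weight of the point.

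Three further inferences are tempting but unsupported:
- *That about 2 of 23 participants would be found to respond, even if all benefit (23 × 9%).* This assumes that a participant counts only when a 95% interval excludes zero. The protocol states no such rule. It plans posterior probabilities of benefit, so the 9% is an illustration of precision and not the yield of the planned analysis.
- *That the Discussion repeats the error* when it says "the individualized nature of the study allows for meaningful intra-participant comparisons". That sentence is qualitative, cites no width and acknowledges uncertainty. Nor do the descriptions of participant feedback use the figure.
- *That differences of about 5 points mark the limit of detection.* From 95%, a 5-point gain is the ceiling of 100%. Gains and losses also differ: a 4-point gain has about 86% power and a 5-point loss only about 66%.

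How 0.117 arose cannot be settled from the document, and the point does not depend on it.

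**Conclusion.** The stated width is wrong as written. On the scale of β₁ it should be about 1.55, roughly 13 times the printed figure. As a risk difference it should be about 0.066, a little over half of it. On both scales the interval is about 6.6 times the assumed effect (1.553/0.234; 6.6 points/1 point), so the individual-level conclusion does not depend on which scale was meant: 600 responses do not resolve a one-point effect in one person.

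This rests on the protocol's own rates and response counts, an even split between conditions, and independent responses within a participant and condition. The population-level sample size of 23 is not affected. This is a numerical error to correct, with a bearing on how the individual part of the primary question is read; it is not a flaw in the design.

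**What to change.** In the Sample size section, replace the figure and name its scale. For example: *with 300 responses per condition, the expected individual 95% interval is about 1.55 wide on the log-odds scale (odds ratio about 0.58 to 2.75 around 1.26), or about 6.6 percentage points wide as a risk difference (about −2.3 to +4.3 around +1 point).* Add that an individual effect of the assumed one-point size cannot reliably be distinguished from no effect; as an illustration, such an interval would exclude zero about 9% of the time.

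If detectable individual effects are stated, give them by direction, with the test used, and not as one symmetric threshold.

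The cost is wording only. No change to the design, the number of participants or the analysis is needed. The downside is that a published precision figure becomes less favourable.

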#### Recruitment

The study population will be recruited from the University of Potsdam and the surrounding community until reaching 23 participants. The study will be advertised on several channels: posters at the university, announcements on the institutional website, email distribution lists, and social media channels (LinkedIn, Instagram). The material will include the title of the study, a short introduction, a contact address, and a reference to the detailed project website. Interested individuals can contact the study team by email promoted in the material. Upon contact, potential participants will receive further information about the study and a short eligibility screening. Eligible individuals will be invited to schedule an on-site appointment. At the beginning of the session, the study purpose and procedures will be explained, and written informed consent will be obtained before participation. A thank you gift in the form of sweats will be offered after finishing the trial, but no course credits nor financial incentives will be given to the study participants.

### Intervention

2.2

#### Description

Within the study, we investigate the effect of listening to music from a self-selected genre compared to no-music condition. At the start of the study, we ask participants to choose the music genre that they anticipate will have the greatest positive impact on their concentration from a preselected list. Participants can choose from fourteen different prespecified genres shown in Table 2, where in three of the genres, the participant can specify whether the lyrics should be in German or English, resulting in a total of 17 different sets of songs. The genres are selected based on their popularity and usage in other studies. With the selection of genres, we tried to cover all five factors of the MUSIC model to a certain extent. By providing German and English lyrics to Alternative-Indie, Rock, and Pop music, we allow the participant to select their own preferences, as lyrics contain speech, which might interfere with the task. As the study is conducted in Germany, it is expected that a subset of participants will prefer German lyrics, while other participants will prefer English lyrics.

For each chosen genre, two well-known songs have been selected by the study team. The songs are chosen based on their popularity within the genre and length (minimum 3 min), and only studio recordings will be selected. Data on attributes of the songs, such as key, pitch, or tempo, are gathered through the open platform *Chosic*. The selected songs will not be disclosed to participants before the trial. For selecting the genre, example songs will be played to the individual so that the participant can select the genre properly. A list of all songs used for intervention can be found in Supplementary Table 1.

**Table 2 tbl2:** Music genres grouped based on the MUSIC factors [13].

Factor	Music genre
Mellow	Ambient
	LoFo-Jazz
	Alternative-Indie^a^, ^b^

Unpretentious	Folk

Sophisticated	Cinematic
	Classic

Intense	Classic-Rock
	Metal
	Rock^b^
	Alternative-Indie^a^, ^b^

Contemporary	EDM
	Hip-Hip
	K-Pop
	Pop^b^
	Techno

a Alternative-Indie could be considered as Mellow and Intense.

b The participant can select English or German lyrics.

During the intervention phases, the songs will be presented in a randomized order. For that, the sound will be played on an external 2.1 speaker system in the room. Study participants control the volume on their own during the study. However, the study team will monitor that the volume does not exceed 80 dB and will be at a minimum of 50 dB.

In the baseline phase, no music and no noise will be played to the study participants.

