## Abstract

**Background::**

Focus and concentration are influenced by various environmental factors, such as listening to music. Recent research highlights the individualized nature of music’s effects on concentration, as responses vary significantly between individuals based on music genres and personal preference. Traditional population-based studies often obscure these between-person differences, while N-of-1 trials, which are individual crossover trials, can provide a personalized approach by allowing each participant to serve as their own control. This study design is particularly suited for examining how self-selected music genres might enhance or alter concentration in each individual. By leveraging an N-of-1 trial design, this study aims to contribute to the growing body of research investigating personalized cognitive interventions, providing insights into individual effects and variations in response to music.

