### Objectives

1.1

This study investigates the effect of music on concentration through a rigorous experimental design, assessing individual changes in attention levels. By including various music genres chosen by the study participants, this study will contribute to understanding the role of music in cognitive performance, ultimately providing insights into whether and potentially how music can enhance concentration.

The study addresses one primary and two secondary research questions.

•*Primary research question:* Does listening to music from a self-selected genre influence cognitive task performance compared with a no-music condition, on average on the population level and for how many individual participants?

Secondary research questions:

1.To what extent can physiological sensor data (e.g., Electroencephalography (EEG), Heart Rate Variability (HRV), Electrodermal Activity (EDA), Eye Tracking) serve as proxies for concentration changes, as measured by the cognitive task?2.To what extent do between-person differences in intervention effects on cognitive task performance be explained by effect modifiers (e.g., music preference, baseline characteristics, physiological traits)?

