#### Primary analysis

To estimate the population-level estimand of interest, we will use a Bayesian generalized linear mixed model (GLMM). The model will include a fixed effect for condition (music vs. no music) and a participant-specific random intercept to account for baseline differences in performance. Hence, it will account for the repeated binary outcomes within participants and individual differences in baseline performance. We will use weakly informative priors to regularize estimates and make prior assumptions explicit. The posterior distribution of intervention effect will be summarized by posterior means/medians, 95% credible intervals, and posterior probabilities (e.g., $\mathrm{Pr}\left(\beta_{1}>0|\text{data}\right)$). Marginal risk differences and odds ratios will be derived from posterior predictive simulations to facilitate interpretation on both the probability and odds scales.

More formally, let $y_{ij}=1$ denote the correct answer in the Stroop task j for individual i and $y_{ij}=0$ denote a wrong answer, respectively. This will be drawn from a Bernoulli distribution with the corresponding probability $p_{ij}$: (3)$$y_{ij}∼\text{Bernoulli}\left(p_{ij}\right)$$

We will use a logistic link, and a fixed effect for the condition $A_{ij}$, where $A_{ij}=1$ denotes listening to music and $A_{ij}=0$ denotes not listening to music, respectively. Further, we will include a random intercept $b_{i}∼N\left(0,\sigma_{b}^{2}\right)$ for each participant i drawn from a normal distribution. (4)$$\text{logit}\left(p_{ij}\right)=\beta_{0}+\beta_{1}\cdot {\text{A}}_{ij}+b_{i}$$

We will use non-informative Priors for the β coefficients following a normal distribution and for $\sigma_{b}^{2}$ a half-student-t distribution with a degree of freedom of 3 and a standard deviation of 1. For the intercept $\beta_{0}$, we choose a large standard deviation to allow a high flexibility: (5)$$\beta_{0}∼N\left(0,5^{2}\right)$$$$\beta_{1}∼N\left(0,1\right)$$$$\sigma_{b}^{2}∼\text{Half-student-t}\left(v=3,\sigma^{2}=1\right)$$

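### The primary model assumes one identical music effect for every participant and recording; if effects vary, the interval for beta1 is too narrow, first for want of a participant-specific music slope and further because recordings are shared

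*Protocol article*

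**What the plan says.** - **Stimuli (Section 2.2, Description).** "For each chosen genre, two well-known songs have been selected by the study team". There are fourteen genres, three of them with a choice of German or English lyrics, which makes 17 song sets. Only the order is random: "During the intervention phases, the songs will be presented in a randomized order".
- **Question (Section 1.1).** "Does listening to music from a self-selected genre influence cognitive task performance compared with a no-music condition". The estimand in Section 2.5 likewise names music from the self-selected genre and averages within-participant differences across participants.
- **Primary model (Section 2.5, Primary analysis, Eq. 4).** "The model will include a fixed effect for condition (music vs. no music) and a participant-specific random intercept". There is no participant-specific music effect and no genre, set or song term.
- **Sensitivity and secondary models (Section 2.5).** These are Fisher's exact test on pooled counts, a chronological time term, and interactions with listening at work and playing an instrument. None adds a music slope or a song term.
- **Power (Section 2.1, Sample size).** "We assumed a correct answer rate of 95% in the no-music condition and 96% across all self-selected music conditions", with the same structure as Eq. (4): one fixed beta1 and a random intercept.
- **Expected heterogeneity (Abstract, Background).** "responses vary significantly between individuals based on music genres and personal preference".

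**The concern.** With 23 participants and 17 sets, some participants must share a set. If a recording helps or distracts, that effect enters the music periods of everyone who hears it. Eq. (4) has nowhere to put it except beta1. The same applies to any difference between people in how they respond to music. The model's standard error reflects only binomial noise and does not grow with either source of variation.

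At stake are the credible interval for beta1, Pr(beta1 > 0) and the marginal risk difference. These would look more certain than the data allow if responses vary as the protocol expects. The participant-by-participant analyses are not affected.

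**Working it through.** **Inputs from the protocol.** Accuracy 95% and 96%; 23 participants; "This yielded about 600 observations per participant across all four periods", so 300 per condition each and 6,900 per condition in total; intercept variance 0.05; power taken as the share of Wald p-values "that were <0.05 across the 5000 series of trials"; 17 sets of two songs.

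**Assumed, because the documents do not give them.** The SD of the participant, song or set effects on the log-odds scale (0.1 to 0.3), and how choices spread over the sets.

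**Step 1: the plan's own power.** beta1 = logit(0.96) − logit(0.95) = 0.2336. SE = sqrt[(1/(0.95×0.05) + 1/(0.96×0.04))/6900] = 0.0826. Power = 1 − Φ(1.96 − 0.2336/0.0826) = 80.7%, and a two-proportion formula gives 80.9%. The protocol states 81.3%, so the figure reproduces, but only with an identical music effect for everyone.

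**Step 2: missing participant slope alone, nothing shared.** If participants' music effects have SD ω, the true SE² = 0.0826² + ω²/23. Coverage of the nominal 95% interval is 2Φ(1.96×0.0826/SE) − 1.

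| ω | True SE | Coverage |
|---|---|---|
| 0.1 | 0.0852 | 94.3% |
| 0.2 | 0.0925 | 92.0% |
| 0.3 | 0.1036 | 88.2% |

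**Step 3: shared songs.** Give each song its own effect with SD τ. Each participant hears two songs, so SE² = 0.0826² + τ²·f/(2×23), with f = Σm²/23 and m the number of listeners per set. For random choice, the expected f is 1 + 22·Σp². That is 2.3 if all 17 sets are equally likely (about 13 used) and 3.95 if popularity falls as 1/rank (about 10 used). With no sharing, f = 1.

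Example at τ = 0.2: the added variance is 0.04×2.3/46 = 0.0020 (even) or 0.04×3.95/46 = 0.0034 (skewed). The SE becomes about 0.094 or 0.101, and the false-positive rate 2[1 − Φ(1.96×0.0826/SE)] is 8.5% or 11%. With f = 1 it is 6.5%.

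The simulation used 20,000 trials per cell, mean music effect zero on the log-odds scale, and 95.5% baseline accuracy. Eq. (4) was approximated by a participant-stratified Mantel-Haenszel test. A participant-level t-test on accuracy differences stood for an analysis with participant-specific effects.

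| Song SD | Eq. (4) type, even | Eq. (4) type, skewed | Participant-level, even | Participant-level, skewed |
|---|---|---|---|---|
| 0 | 5% | 5% | 5% | 5% |
| 0.1 | 6% | 7% | 6% | 6% |
| 0.2 | 9% | 11–12% | 7% | 9% |
| 0.3 | 16–17% | 20–21% | 10% | 14% |

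With almost no sharing (400 sets), the Eq. (4)-type rate at SD 0.2 is 7%. At SD 0.3, part of the rate arises because a zero mean on the log-odds scale is not exactly zero on the risk scale. With the mean risk difference set to zero, the Eq. (4)-type rates there are 13% and 18%, as the SE formula also gives.

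**Step 4: effect common to both songs of a set (set SD τ).** SE² = 0.0826² + τ²·Σm²/23². Even means six sets of two and eleven of one (Σm² = 35). Concentrated means 8, 6, 4, 3 and 2 on five sets (Σm² = 129).

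| Set SD | Coverage, no sharing | Even | Concentrated |
|---|---|---|---|
| 0.1 | 94.3% | 93.9% | 90.8% |
| 0.2 | 92.0% | 90.4% | 79.1% |
| 0.3 | 88.2% | 84.8% | 66.0% |

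Fitting the random-intercept model by maximum likelihood at set SD 0.2 (500 runs each, no mean effect) gave coverage of 90.4%, 89.6% and 77.2%.

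**The case against.** A reader might infer that the plan wrongly treats the music effects of participants who share a genre as independent, and that the interval is therefore certainly too narrow. The documents do not support this, for four reasons.

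- **Model.** Eq. (4) contains no participant-specific music effects that could be independent or not. It assumes a single common effect, and the missing slope narrows the interval even when nobody shares a song. In three genres, sharing also needs the same lyrics language.
- **Target.** The abstract describes the intervention as a playlist of preselected songs, and the estimand averages across participants. If the fixed playlists are the intervention, genre choice is part of each participant's draw and sharing adds no variance. The genre wording of the question and estimand favours the wider target but does not settle it. Read literally as an average over the enrolled participants only, the estimand would make the missing slope matter less too.
- **Variance.** No song variance is given. The introduction cites a study in which fondness mattered rather than type of music, which points to differences between people. An SD such as 0.42, with rates near 30%, would be almost twice the planned beta1 of 0.234 and has no support in the documents.
- **Size.** At song SD 0.1 to 0.2, an analysis with participant-specific effects rejects in only 6% to 9% of null trials.

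All four stand as limits on the claim. They do not remove it. The protocol expects effects to vary, no planned population-level model lets them vary by participant or recording, and nowhere is the conclusion restricted to the listed recordings.

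**Conclusion.** The point holds in a conditional form. If music effects vary between people or recordings, Eq. (4) gives too narrow an interval for a population-level effect. The missing participant slope is the first cause. Shared recordings are a second and separate one, and they count only if the conclusion is meant to reach beyond the chosen songs.

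At an assumed song SD of 0.1 to 0.3, the nominal 5% error becomes about 6% to 17% (even choice) or 7% to 21% (skewed choice). The upper ends fall to 13% and 18% once the risk-scale artefact is removed. Sharing on its own leaves about 6% to 10% or 6% to 14% in an analysis that already has participant-specific effects, which is 1 to 5 or 1 to 9 points above nominal. The loss is small at SD 0.1 with an even spread and large only if effects are sizeable or choices concentrate on a few sets. Neither the SD nor the spread of choices can be taken from the documents.

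**What to change.** 1. Add a participant-specific music slope to Eq. (4): logit(p_ij) = β0 + β1·A_ij + b_i + A_ij·d_i, with d_i ~ N(0, ω²), and derive the marginal risk difference over these slopes.
2. Log which recording plays in each music period.
3. Prespecify a sensitivity analysis that adds A_ij·s_k, with k the recording or the song set. Put the prior on the SD and scale it to plausible log-odds effects, and report results under at least one other prior scale.
4. Otherwise, state that the population-level conclusion applies to the listed recordings.

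A song term without the participant slope would not do, and nor would reusing the half-Student-t prior that the protocol places on the intercept variance. Read as scale 1 with 3 degrees of freedom, that prior has median 0.76 for the variance, an SD of 0.87. In an approximate check with no song effect at all, a model with a song term, this prior and no participant slope reported a song SD of about 0.20. It widened the posterior SD of beta1 from 0.082 to 0.093–0.098. With participant slopes of SD 0.3 and no song effect, it reported a song SD of about 0.26.

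**Cost.** A few model terms and a logged variable; no extra participants or measurements. The interval widens somewhat: at song SD 0.2 the SE of beta1 rises from 0.083 to about 0.094–0.102. Power at beta1 = 0.2336 is then 1 − Φ(1.96 − 0.2336/SE), about 70% to 63%. With about two listeners per song in use (23/13 = 1.8), the song variance is weakly identified and its prior will matter.
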